**Figure 2 fig2:**
[figure not shown]
Flow chart of patient recruitment and study implement.

**Table 1 tab1:** Timeline for study enrollment, intervention, and evaluation.

	Study period						
	Recruitment	Allocation	Intervention		Follow-up		
Timepoint	-T1	0	Month 0	Month 3	Month 6	Month 9	Month 12
Enrollment							
Informed consent	√						
Eligibility screen	√						
Allocation		√					
Intervention							
HAPA-mHealth							
Control							
Assessments							
Sociodemographic variables			√				
Proportion of individuals adopting health behaviors			√	√	√	√	√
Knowing rate of health knowledge			√	√	√	√	√
Refill and medication adherence scales			√	√	√	√	√
Quality of life			√	√	√	√	√
Depression and anxiety			√	√	√	√	√
Perceived stress scale			√	√	√	√	√
Perceived social support			√	√	√	√	√
Satisfaction				√	√	√	√

### Study setting, randomization and blinding

2.2

The study will be a single-center, single-blind randomized controlled trial conducted at the Fourth Central Hospital of Baoding City, Hebei Province. Convenience sampling will be employed to recruit patients diagnosed with brucellosis. In this study, patient enrollment was conducted in batches to ensure feasibility, sample balance, and control of potential confounding factors. Specifically, eligible patients were enrolled in batches based on established time points, screening criteria, and enrollment procedures to ensure the study’s orderly and efficient progress.

Randomization was performed using Excel software to ensure unbiased group allocation. A new worksheet was created with numbers 1 to *N* in column A, where *N* represents the total number of participants. In column B, the formula = RAND() was used to generate random numbers between 0 and 1 for each participant. These random numbers were then fixed by copying and pasting them as ‘values’ to prevent modifications. The participants were then sorted by their random numbers in ascending order, and group assignments were made accordingly. The random allocation sequence will be generated by the researchers.

A single-blind design was implemented to ensure blinding. Participants were blinded to their group allocation, while evaluators remained aware of the group assignments. Allocation concealment was achieved using the envelope method. Adequate opaque envelopes were prepared, each labeled with a unique identifier number. A small slip of paper containing group assignment information was placed inside each envelope and sealed. After enrollment, participants received envelopes in sequential order based on their numerical identifiers and opened them independently to reveal their group assignment. The distribution and opening of envelopes were supervised by a designated individual to ensure the integrity of allocation concealment, and the process was documented for transparency. Unused envelopes were securely stored to preserve allocation concealment and maintain the single-blind design.

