### Outcomes measure

2.8

Medical staff will distribute the questionnaire via the Questionnaire Star web platform. Patients will complete it online, receiving instructions either in person (during hospitalization) or by phone (after discharge). Demographic information will be collected through the case system and self-designed questionnaires (Table 1).

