##### Data disclosure and blinding

2.10.1.4

This study employs a single-blind design, where participants are unaware of their group assignments, while the researchers are informed. Prior to data analysis, the researchers will ensure that the blinding is maintained. All group allocation information will be provided to the relevant personnel in sealed envelopes after the completion of the study. Data analysis will be conducted by an independent statistical analysis team, and the team will not be involved with the group allocation information during data processing and analysis to ensure the impartiality of the results.

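### The trial is labelled single-blind with participants unaware, but participants open the envelope that shows their arm and evaluators know it too, so the self-rated outcomes are reported and assessed unblinded

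*Protocol article*

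**What the plan says.** The abstract and section 2.2 call the trial single-blind. Section 2.2 defines this: "Participants were blinded to their group allocation, while evaluators remained aware of the group assignments". Section 2.10.1.4 repeats it: "This study employs a single-blind design, where participants are unaware of their group assignments, while the researchers are informed".

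Section 2.2 also describes how allocation is disclosed. On the envelopes: "A small slip of paper containing group assignment information was placed inside each envelope and sealed". On their use after enrolment: "participants received envelopes in sequential order based on their numerical identifiers and opened them independently to reveal their group assignment". A designated person supervises and the process is documented.

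Section 2.10.1.4 adds: "All group allocation information will be provided to the relevant personnel in sealed envelopes after the completion of the study". It then says that an independent statistical team will work without the allocation information.

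Under section 2.8, medical staff distribute the questionnaire, patients complete it online, and instructions are given in person or by telephone. Section 2.8.1 names two primary outcomes: the proportion adopting health behaviours (a self-rated frequency scale with a threshold score of 70) and the knowledge rate (items marked correct, or incorrect/unknown).

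**The concern.** A participant who reads a slip naming the group is not blind to the group, so the single-blind label describes a protection that the design does not have. Evaluators are openly unblinded, and no other party to outcome reporting or assessment is described as blind.

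The consequence is sharpest for the behaviour outcome. In the mHealth arm, clinicians coach hygiene and other health behaviours and ask for a diary of them; the same patients then rate how often they carry out protective and hygiene measures, knowing that they were coached. The limitations paragraph in section 3 concedes social-desirability and recall bias, but as a general feature of self-report. With allocation known, the bias can act more strongly in one arm, and it then enters the treatment difference directly. A reader or risk-of-bias assessor who relies on the label would credit the trial with the safeguard that is absent.

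**Working it through.** **Text check.** The protocol states no figure on this point, so the first step is to set the statements side by side.

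| Party | Stated status | What the text describes |
|---|---|---|
| Participants | Unaware (2.2, 2.10.1.4) | Open their own envelope and read their group (2.2) |
| Evaluators, researchers | Aware (2.2, 2.10.1.4) | Same |
| Statistical team | Kept from allocation (2.10.1.4) | Nothing contradicts this |

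The first row is a contradiction within one paragraph of section 2.2. Removing the envelope step would not rescue the label. The mHealth arm receives 10 minutes of physician guidance by WeChat every Monday and daily reminders (2.5.1.2.1). The control arm receives a brochure, a telephone follow-up after discharge and a further follow-up at 3 months (2.5.2). Both arms receive printed material, so the WeChat contact is the visible difference. No sham or attention control is described, and consent involves explaining the nature and scope of the trial (2.10.3.2).

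**Which outcomes are exposed.** The behaviour scale (2.8.1.1) and the secondary scales (2.8.2: medication adherence, quality of life, anxiety and depression, stress, social support, satisfaction) are self-rated. The knowledge items (2.8.1.2) are scored against a correct answer, so favourable reporting alone cannot raise that score.

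**Illustration of size.** The bias is an assumption, shown as a range.

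Inputs from the protocol: 60% adoption in control, a planned 30-point difference (90% against 60%), 29 per arm randomised, 23 per arm after losses (2.4), two-sided 0.05 (2.9). Assumed: no true effect, and reported adoption inflated by b in the mHealth arm only.

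With p2 = 0.60, p1 = 0.60 + b and p̄ = (p1 + p2)/2, the chance of a significant result favouring mHealth is, by the normal approximation with pooled variance,

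Φ{[b√n − 1.96√(2p̄(1 − p̄))] / √(p1(1 − p1) + p2(1 − p2))}.

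For b = 0.10 and n = 29: p̄ = 0.65 and b√n = 0.10 × 5.385 = 0.5385. Then 1.96 × √0.455 = 1.322, and the denominator is √(0.21 + 0.24) = 0.671. The argument is (0.5385 − 1.322)/0.671 = −1.168, and Φ = 0.121.

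| Inflation b | Patients of 29 (b × 29) | n = 29 per arm | n = 23 per arm |
|---|---|---|---|
| 0 | 0 | 0.025 | 0.025 |
| 5 points | 1.5 | 0.058 | 0.053 |
| 10 points | 2.9 | 0.121 | 0.105 |
| 15 points | 4.4 | 0.227 | 0.188 |
| 20 points | 5.8 | 0.380 | 0.311 |

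On the scale of the planned effect, 5 to 20 points is 5/30 = 17% to 20/30 = 67% of the difference that the trial was sized to find.

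**The case against.** The strongest reply is that a WeChat coaching trial cannot readily blind its participants, so an open design is no fault, and no planned analysis or sample size changes. That stands: the error lies in claiming blindness, not in lacking it.

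It might also be said that participants are blind in the sense of not knowing which arm is under test. The text does not say so. It says that they are unaware of their group assignment, which is what the envelope reveals.

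Several stronger readings are tempting but not supported:

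- **Nobody at all is blind.** Section 2.10.1.4 keeps the statistical team from the allocation. That is real blinding, though it cannot correct biased answers.
- **Both primary outcomes are equally affected.** The knowledge test is scored right or wrong.
- **The release sentence in 2.10.1.4 flatly contradicts 2.2.** It names relevant personnel, not participants, and stands next to the text on data analysis. It can be read as a rule for the analysis team. As written it is unclear, because envelopes are opened after enrolment and researchers are said to be informed, but clarification is enough.
- **Concealment is broken.** Section 2.2 says "The random allocation sequence will be generated by the researchers". It does not say that these researchers enrol patients or hold the list at recruitment, and the envelopes are opaque, sealed, numbered, issued in sequence and supervised.
- **Treating clinicians coach the answers.** Section 2.8 says that medical staff distribute the questionnaire; it does not say who gives the instructions.

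**Conclusion.** The point holds for participants and evaluators. By the protocol's own account both know the allocation, so single-blind is a wrong description in the abstract, section 2.2 and section 2.10.1.4. It should be corrected, because it bears on what the self-rated behaviour outcome can support. The knowledge outcome is less exposed, and the blinding of the analysts is not in dispute.

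The size is unknown. The range of about 6% to 38% at 29 per arm (about 5% to 31% at 23) rests on the assumptions of no true effect, 60% adoption in both arms, inflation of 5 to 20 points in the mHealth arm only, and a normal approximation. It shows how sensitive a trial of this size is to a few favourable answers; it does not estimate the bias that will occur.

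**What to change.** 1. In the abstract, 2.2 and 2.10.1.4, describe the trial as open-label for participants and evaluators, with blinded statistical analysis only. Delete the statements that participants are unaware of their group.
2. Reconcile the sentence in 2.10.1.4 on release after study completion with the envelopes opened after enrolment and the informed researchers. If it is meant for the analysis team, say so; do not simply delete it, since it may be the only statement of when allocation is released.
3. Put the questionnaire instructions as fixed text in the existing online form, so that all patients get the same wording whoever contacts them.
4. In the limitations in section 3, state that self-report bias may differ by arm because allocation is known, and that this applies chiefly to the behaviour outcome and the self-rated scales.
5. Do not give list generation or envelope preparation to the independent statistical team: that would unblind the one party kept from the allocation. If the task is reassigned, use existing staff who take no part in enrolment or analysis.

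The cost is rewording and a small change to the online form. Sample size, intervention and endpoints stay as they are. The downside is a less favourable blinding label.

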### Study participants

2.3

The study was approved by the Ethics Committee of Baoding No. 4 Central Hospital. Participants will be patients from Baoding No. 4 Central Hospital, located in Baoding City, Hebei Province, China. Recruitment of study participants is expected to begin in December 2024. After enrolling in the trial and signing the informed consent form through face-to-face communication at the hospital, each participant will begin the formal trial intervention. Therefore, participants will be recruited and begin the intervention at different times. They will all complete the 3-month intervention cycle.

#### Inclusion criteria

2.3.1

(1) Patients aged ≥18 years(2) The patient is a permanent resident of Hebei Province (annual time away from home is less than 1 month).(3) All patients meet the relevant diagnostic criteria for brucellosis in the Brucella Disease Diagnostic and Treatment Guidelines and the diagnosis of brucellosis was confirmed by pathological examination (47);(4) The patient’s daily use of a smartphone and familiarity with general WeChat functions;(5) Patients voluntarily agree to participate in the study by signing the informed consent form.

#### Exclusion criteria

2.3.2

(1) The patient has no fixed contact information, no family member to act as a contact, and cannot be easily reached by phone or WeChat.(2) The patient is currently taking psychotropic medication.(3) The patient exhibits mental symptoms, such as confusion, slurred speech, or uncooperativeness(4) The patient has serious comorbidities or physical impairments.(5) The patient has participated in other clinical trials(6) Pregnant or breastfeeding women(7) Any other reasons deemed unsuitable for participation in the trial.

### Sample size

2.4

This study is a randomized controlled trial with two groups: the mobile health intervention group and the conventional education group. The primary outcome is the health behavior formation rate among the participants. Based on a literature review (48), the compliance rate for behavior formation in the mobile health intervention group is expected to be 90%, compared to 60% in the control group. The significance level is set at *α* = 0.05, with a 90% confidence level. Using PASS15 software, the sample size for the intervention group was calculated as N1 = 23, and for the control group, N2 = 23. Considering a 20% follow-up loss rate, at least 29 participants are required in each group, resulting in a total of 58 participants.

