### Statistical analysis

2.9

Statistical analyses will be performed using SPSS Statistics 26.0 software. Count data will be expressed as the number of cases and rate (%), while measurement data will be presented as mean ± standard deviation. Before performing parametric tests, normality assumptions will be tested using the Shapiro–Wilk test. If data is normally distributed, parametric tests, such as the independent *t*-test, may be used. However, if the normality assumption is violated, non-parametric tests, such as the Mann–Whitney U test, will be used to compare changes in scale scores between baseline and endpoint between the two groups. The Wilcoxon signed-rank test will be employed for within-group comparisons of scale scores between baseline and endpoint. Demographic and clinical characteristics at baseline will be summarized descriptively for each group. Categorical variables will be reported as counts and percentages, and continuous variables as mean ± standard deviation.

For the primary analysis, all randomized participants will be included in an intention-to-treat (ITT) analysis, regardless of whether they complete the intervention. For secondary analyses, only participants who complete the intervention and follow-up will be included in a per-protocol (PP) analysis.

Regarding missing data, we will explore the missing data and compare the distribution of key variables. If the missing data is reasonable in amount and assumed to be Missing at Random (MAR), multiple imputation methods will be used to handle the missing data for both ITT and PP analyses. This ensures that the handling of missing data is consistent across both analysis groups. Baseline variables will be used as auxiliary variables for imputation, and multiple imputed datasets will be generated. Linear regression and logistic regression will be applied to analyze the imputed datasets, and the results will be pooled to provide final estimates and standard errors. A two-sided test will be used, and statistical significance will be defined as *p* < 0.05. The detailed statistical analysis plan for this study is available for public access at the Chinese Clinical Trial Registry: ChiCTR Statistical Analysis Plan (https://www.chictr.org.cn/showproj.html?proj=196659).

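### The 23 per arm in section 2.4 does not follow from the stated inputs under the two-sided 5% rule; power is about 69% with 23 evaluable per arm and 78% with 29 (chi-square)

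*Protocol article*

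**What the plan says.** Section 2.4 (Sample size) names the health behaviour formation rate as the primary outcome. It expects 90% in the mobile health arm, "compared to 60% in the control group". The error rates are given in one sentence: "The significance level is set at *α* = 0.05, with a 90% confidence level". Neither the word power nor the sidedness of the test appears there. From PASS15, "the sample size for the intervention group was calculated as N1 = 23, and for the control group, N2 = 23". The allowance for loss follows: "Considering a 20% follow-up loss rate, at least 29 participants are required in each group, resulting in a total of 58 participants".

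Section 2.9 (Statistical analysis) sets the decision rule: "A two-sided test will be used", with significance at p < 0.05. It makes the primary analysis intention-to-treat on all randomised participants, with multiple imputation where missingness is judged to be at random.

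**The concern.** A sample-size statement should let the reader recover the number from the inputs. Here it does not. The 90% stands where power normally stands, and most readers will take it as power. At 90% versus 60% with a two-sided 5% test, 23 per arm is well short of that.

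This calculation is the only justification given for 58 participants. A reader who believes the trial has 90% power for a 30-point difference would take a non-significant result as fair evidence against an effect of that size. With 23 evaluable per arm, a chi-square test would miss such an effect about three times in ten.

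**Working it through.** **Inputs.** p1 = 0.90, p2 = 0.60 and alpha = 0.05 (section 2.4); two-sided (section 2.9); 1:1 allocation; 20% loss (section 2.4). The difference is 0.30, and its square is 0.09.

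- Unpooled variance term: 0.90×0.10 + 0.60×0.40 = 0.33
- Pooled variance term: 2×0.75×0.25 = 0.375

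**Formulas, n per arm.**

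- Unpooled: n = (z_alpha + z_power)² × 0.33 / 0.09
- Pooled: n = (z_alpha×√0.375 + z_power×√0.33)² / 0.09

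**Trying to reproduce 23.**

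| Setting | z_alpha | z_power | Unpooled n | Pooled n |
|---|---|---|---|---|
| Two-sided 0.05, 90% power | 1.960 | 1.282 | 38.5 → 39 | 41.7 → 42 |
| Two-sided 0.05, 80% power | 1.960 | 0.842 | 28.8 → 29 | 31.5 → 32 |
| Two-sided 0.05, 70% power | 1.960 | 0.524 | 22.63 → 23 | 25.05 → 26 |
| One-sided 0.05, 90% power | 1.645 | 1.282 | 31.4 → 32 | 33.8 → 34 |
| One-sided 0.05 (= two-sided 0.10), 80% power | 1.645 | 0.842 | 22.67 → 23 | 24.7 → 25 |

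Two rows give 23, both with unpooled variance: one-sided 0.05 (two-sided 0.10) with 80% power, and two-sided 0.05 with about 70% power. Neither power is stated in section 2.4. At two-sided 0.05, neither 80% nor 90% power gives 23.

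**Power at two-sided 0.05, by normal approximation.**

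- Unpooled, n = 23: the standard error is √(0.33/23) = 0.1198. Then 0.30/0.1198 − 1.960 = 0.545, giving 70.7%.
- Pooled, n = 23: the null standard error is √(0.375/23) = 0.1277. Then (0.30 − 1.960×0.1277)/0.1198 = 0.415, giving 66.1%.
- Unpooled, n = 29: 0.30/0.1067 − 1.960 = 0.852, giving 80.3%.
- Pooled, n = 29: (0.30 − 1.960×0.1137)/0.1067 = 0.723, giving 76.5%.

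**Exact power.** This sums the binomial probabilities of every pair of counts that the test declares significant at two-sided 0.05.

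| Evaluable per arm | Chi-square (no correction) | Fisher |
|---|---|---|
| 23 | 68.9% | 57.5% |
| 29 | 77.8% | 68.1% |

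**Loss step.** 23/(1 − 0.20) = 28.75, rounded up to 29, so 58 in total. This step is correct.

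**For comparison.** Inflating the 90%-power sizes in the same way gives 39/0.8 = 48.75 → 49 and 42/0.8 = 52.5 → 53 per arm, or 98 to 106 in total.

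**The case against.** Four objections deserve an answer.

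1. **Section 2.4 never says power.** This is true. Calling 90% the claimed power is an interpretation, though the natural one. The literal reading does not rescue the text: a 90% confidence level corresponds to two-sided alpha 0.10, which contradicts alpha = 0.05 in the same sentence and the rule in section 2.9, and it leaves the calculation with no stated power.

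2. **A reader might infer that the sponsor ran a one-sided test at 80% power.** The documents do not support this. Two-sided 0.05 with about 70% power also rounds up to 23, and the PASS15 settings are not shown. The match shows what is compatible with 23, not what was done.

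3. **Quoting only the 23-per-arm power is pessimistic.** This also stands. The primary analysis is intention-to-treat with multiple imputation, and section 2.6 plans to collect data from participants who stop. Effective information should lie between 23 and 29 per arm, so a flat statement that real power is 58-71% would be too strong. The Fisher figures also depend on a test that the article does not name; section 2.9 mentions logistic regression for imputed data.

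4. **The Discussion calls the trial exploratory and admits a small sample.** It does, but it links the small sample to representativeness. It does not say that power is limited, so it does not correct section 2.4.

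**Conclusion.** The point holds as a conflict between stated figures. Given 90% versus 60% and the two-sided 5% rule, 23 per arm is 16 to 19 short of what 90% power needs (39 to 42) and 6 to 9 short of what 80% power needs (29 to 32). The confidence-level phrase is wrong on either reading.

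Depending on how much follow-up is recovered, an unadjusted chi-square comparison has about 69% to 78% power. The corresponding Fisher range is 57% to 68%. Even with no loss at all, none of these tests reaches 90%.

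These figures assume that the expected rates are right, that allocation is equal, and that the analysis is a simple comparison of two proportions. Which settings produced 23 cannot be determined from the article, and the conclusion does not depend on knowing them.

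**What to change.** Keep 58 participants and correct section 2.4:

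- Delete "with a 90% confidence level".
- State that alpha is two-sided 0.05, in line with section 2.9.
- Name the test and the variance formula assumed in the calculation.
- Give the resulting power across the plausible range. For example: with expected rates of 90% and 60% and a two-sided alpha of 0.05, an unadjusted chi-square comparison has about 69% power with 23 evaluable participants per arm and about 78% with 29. If the primary comparison will use another test, recompute for that test.
- Add to the limitations in the Discussion that power for the expected difference is limited, so a non-significant result would not rule it out.

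The cost is a rewording and a less favourable stated power; no further participants are needed. If the sponsor does want 90% power, the price is 98 to 106 participants after 20% loss. That should be an open choice.
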